## Abstract

**Introduction:**

Dissemination of results of randomised controlled trials is traditionally limited to academic and professional groups rather than clinical trial participants. While there is increasing consensus that results should be communicated to trial participants, there is a lack of evidence on the most appropriate methods of dissemination. This study within a trial (SWAT) aims to address this gap by using a public and patient involvement (PPI) approach to identify, develop and evaluate a patient-preferred method of receiving trial results of the Thyroid Hormone Replacement for Subclinical Hypothyroidism Trial (TRUST).

**Methods:**

An experimental (intervention) study will be conducted using mixed methods to inform the development of and evaluation of a patient-preferred method of communication of trial results. The study will involve three consecutive phases. In the first phase, focus groups of trial participants will be conducted to identify a patient-preferred method of receiving trial results. The method will be developed and then assessed and refined by a patient and public expert group. In the second phase participants will be randomly assigned to the intervention (patient-preferred method) and comparison groups (standard dissemination method as developed by the lead study site in Glasgow, Scotland). In the third phase, a quantitative questionnaire will be used to measure and compare patient understanding of trial results between the two groups.

**Discussion:**

This protocol provides a template for other trialists who wish to enhance patient and public involvement and additionally, will provide empirical evidence on how trialists should best disseminate study results to their participants.

## Background

1

Dissemination of trial results has traditionally been limited to three channels: scientific meetings and peer reviewed publications and texts; lay media; and groups and organizations with a particular health interest [1]. However, the most recent iterative of the EU Clinical Trials Regulation 536/2014 (Article 37) requires sponsors to provide summary results of clinical trials in a format understandable to laypersons [2]. Therefore, disclosure of study results to trial participants is now a mandatory fourth channel of dissemination. While it is desirable that results are shared with study participants, there is a lack of evidence on the most appropriate methods of sharing research findings with these important stakeholders [1]. Since the findings exist in a context of scientific exchange and debate, researchers need to ensure that the information presented to participants meets their needs [1].

The move to disseminate trial results to trial participants had occurred contemporaneously with the expanding role of Patient and Public Involvement (PPI) in research. The Involve (UK) definition of PPI is widely used and defines public involvement in research as research being carried out ‘with’ or ‘by’ members of the public rather than ‘to’, ‘about’ or ‘for’ them [3]. The goal of PPI is to achieve a true partnership between public/patients and researchers, leading to improved research quality, relevance and outcomes. While PPI is gathering considerable momentum internationally, limited attention has been placed on measuring the impact of PPI [5], [6]. Research in this area has often found to be of poor quality and there have been difficulties in identifying the exact contribution patient involvement has on overall patient care [7]. For these reasons a clear need has been established to measure the impact of PPI in a valid, reliable and responsive way [5].

This study within a trial (SWAT) aims to address the lack of evidence on the most appropriate methods of sharing research findings with trial participants by using a PPI approach to identify, develop and evaluate a patient-preferred method of receiving trial results within the Thyroid Hormone Replacement for Subclinical Hypothyroidism Trial (TRUST).

The TRUST clinical trial is a multi-centre, double blind, placebo controlled, phase III clinical trial testing the efficacy of thyroxine replacement in subclinical hypothyroidism in older community dwelling adults. The study sites for the trial are the University of Glasgow, Scotland (lead site); Leiden Academy on Vitality and Ageing, The Netherlands; Leiden University Medical Centre, The Netherlands; University of Berne, Switzerland; and University College Cork, Ireland. This collaborative academic study recruited 738 participants with subclinical hypothyroidism (SCH) over a three-and-a-half-year period from 2013 to 2017 [4]. A total of 115 participants were recruited in Ireland. The TRUST Trial completed recruitment in November 2016 and the results will be reported in Spring 2017.

## Methods

2

**Study Design:** This study will adopt an experimental (intervention) design using mixed methods to inform the development of and evaluation of a patient-preferred method of communication of trial results. The design consists of three distinct phases (see Fig. 1).

**Fig. 1 fig1:**
[figure not shown]
Study Design.

**Setting:** The study will be conducted at the Irish TRUST site. The hub centre for the Irish site was located at the Mercy University Hospital, Cork with five satellite sites located at Waterford University Hospital, Bantry General Hospital, Kerry General Hospital, St John's Hospital Limerick and Vista Primary Care Centre, Naas. A total of 115 participants were recruited from these Irish sites and randomised to the TRUST Trial.

**Population:** As this is a SWAT within the TRUST trial, the study sample is determined by the trial. This study will consist of all TRUST participants recruited in the Irish site (n = 115).

### Phase one: qualitative data collection

2.1

**Aim:** To use a PPI approach to explore participants' perspectives and preferences of result dissemination. This information will identify and guide the development of the PPI informed result dissemination method.

**Design:** Qualitative focus group study.

Method:

#### Focus groups

2.1.1

Three semi-structured focus groups will be conducted with four to eight TRUST participants per focus group. Participants for this phase will be determined based on the geographical feasibility of carrying out the focus groups. Cork is the main site for TRUST in Ireland therefore all Cork-based patients (n = 38) will be contacted via letter and invited to participate in one of three focus groups in the Cork TRUST site. The sessions will be led by an independent qualitative researcher. A topic guide will be used to guide the focus groups. The Consensus-Oriented-Decision-Making (CODM) model will be used in order to guide the group to reach a consensus. The CODM model steps [8], [9] include:1Framing the topic2Open discussion3Identifying underlying concerns4Collaborative proposal building5Choosing a direction6Synthesizing a final proposal7Closure.

**Analysis:** Focus group recordings will be transcribed verbatim and entered into NVivo Version 11 for thematic analysis. Braun and Clarke [9] guidelines will be followed when thematic analysis is being performed. Identified themes will be used to model a patient-preferred method for the dissemination of results.

#### Patient and public expert group

2.1.2

A patient and public expert group will be established to assess the content on and test the validity of the proposed trial result dissemination method. This group will consist of three to five TRUST participants recruited from the Cork site. A series of consultations will take place with this group in order to iteratively refine the format of the patient-preferred dissemination method.

**Outcome:** The findings from this phase will be used to identify and develop the patient-preferred end-of-trial result dissemination method.

### Phase two: intervention

2.2

**Aim:** To disseminate the results of the TRUST Trial to TRUST participants.

**Design:** A prospective, randomised, single-blind, parallel-group intervention group trial.

**Method:** Results will be disseminated to participants in Ireland after the final results of the trial are published in April 2017. Simple random allocation will be used to randomise participants to the intervention or comparison group. Participants from the patient and public expert group (n = 3) will not be randomised as they will have already reviewed the content of the intervention method prior to randomisation. The intervention group will receive the PPI informed dissemination method and the comparison group will receive the standard dissemination method developed by the lead study site in Glasgow, Scotland. Participants will be blinded to the result method they will receive. One member of the research team will be un-blinded in order to perform the randomisation and distribute the results of the trial.

**Outcome:** All TRUST participants will receive the results of the TRUST Thyroid Trial.

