### Phase three: quantitative data collection

2.3

**Aim:** To measure the impact of PPI on patient understanding of end-of-trial results.

**Design:** Quantitative questionnaire evaluation of the intervention.

**Method**: A questionnaire will be developed and validated to measure patient understanding of the end-of trial results. The questionnaire will be developed in consultation with experts in the area of subclinical hypothyroidism and scale development. It is expected that the questionnaire will contain no more than 10 items which will be measured on a LIKERT scale. While there is debate in the literature regarding the minimum required sample size for exploratory factor analysis, it has been established that a ratio of 10 participants per variable is appropriate to produce solutions that are accurate representations of the population parameters [10]. Questionnaire items will be developed by adapting existing questionnaires and new items will be generated where necessary through consultation with the content and scale development experts and the patient and public expert group. Prior to administering the full questionnaire, it will be reviewed by the patient and public expert group to assess content and face validity. Any suggestions and changes made by this group will be incorporated into the final questionnaire. The questionnaire will be sent to the intervention and comparison groups one week after they have received the results of the trial.

**Analysis:** Completed questionnaires will be entered into SPSS software. The psychometric properties and construct validity of the questionnaire will be examined with exploratory factor analysis, using principal component analysis (PCA). PCA is a useful exploratory factor analytic tool that can be incorporated into the development and refinement of new scales [11]. In this case, PCA will allow for the maximum amount of variance in patient understanding to be explained by the smallest number of constructs. Internal consistency of the questionnaire will be investigated using Cronbach's alpha coefficient. Where possible, participant responses will be analysed using descriptive and inferential (Chi-square test) statistics. The researcher carrying out the input and analysis of this data will be blinded to the participants' allocation status. Subgroup analysis will also be conducted to measure how patient understanding is impacted by age, gender, education status and study site attended.

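### Simple randomisation of 110 to 112 patients, all listed beforehand, is valid but leaves avoidable chance imbalance in site and focus-group attendance, which the one named test does not adjust for

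*Protocol article*

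**What the plan says.** Phase two, Method, fixes the allocation: "Simple random allocation will be used to randomise participants to the intervention or comparison group". No ratio, block or stratum is named.

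The patients are known in advance. Under Population: "As this is a SWAT within the TRUST trial, the study sample is determined by the trial". That sample is the 115 Irish participants. Background adds: "The TRUST Trial completed recruitment in November 2016 and the results will be reported in Spring 2017". Results go out only after publication in April 2017.

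Prior involvement is treated in two ways. On the expert group: "Participants from the patient and public expert group (n = 3) will not be randomised", because its members will have seen the intervention content. On the focus groups: "Three semi-structured focus groups will be conducted with four to eight TRUST participants per focus group". All attenders are drawn from the 38 Cork-based patients, and their themes are used to model the intervention. They are neither excluded from randomisation nor balanced.

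Phase three, Analysis, names chi-square as the inferential test and adds: "Subgroup analysis will also be conducted to measure how patient understanding is impacted by age, gender, education status and study site attended".

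**The concern.** The main practical advantage of simple randomisation over a restricted list is that the next assignment cannot be guessed while patients enrol one by one. Here no enrolment remains, so a restricted list gives up nothing in concealment.

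The protocol treats site as relevant to understanding, and it treats close involvement with the intervention as a reason to exclude the expert group. Yet site and focus-group attendance are left to chance. The sample cannot be enlarged, the article describes no baseline measure of understanding, and the named test takes no covariates. If one arm happens to hold more Cork patients or more attenders, the single primary comparison is harder to interpret, and the planned site subgroups may be lopsided.

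**Working it through.** **Inputs from the article**
- Randomised: 115 − 3 = 112. The expert group is set at 3 in Phase two, but section 2.1.2 says "This group will consist of three to five TRUST participants recruited from the Cork site"; with 5 it is 115 − 5 = 110.
- Cork patients left: 38 − 3 = 35 (33 if 5 are removed).
- Focus-group attenders: 3 × 4 = 12 to 3 × 8 = 24.
- Sites: one hub and five satellites.

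**Assumptions**
- The 38 Cork-based patients are the hub-site patients.
- Satellite sizes are not given; (115 − 38)/5 = 15.4, so about 15 each.
- The prevalence of lower education is not given; 30% to 50% is used.

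The article states no power or balance figure to reproduce.

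**1. Arm size.** One arm is Binomial(112, 0.5), SD = √(112 × 0.25) = 5.3, 95% range 46 to 66. P(arms differ by 12 or more) = 0.299. The cost is small:
- Efficiency relative to 56:56 is 4·n₁·n₂/n².
- For 50:62 it is 4 × 50 × 62/112² = 0.989.
- For 46:66 it is 4 × 46 × 66/112² = 0.968.
- On average it is 1 − 1/112 = 0.991.
- At the difference giving 80.0% power at 56:56 (0.53 SD, two-sided 5%, both assumed), power at 46:66 is 78.7%.

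**2. Cork share.** With p = 35/112 = 0.3125, the SD of the between-arm difference is about √(0.3125 × 0.6875 × 2/56) = 0.088. Then 0.10/0.088 is about 1.14, a two-sided probability of about 0.25. Simulation (100,000 draws) gives 0.26, and 0.09 for 15 points or more. An unstratified 56:56 list still gives 0.22, so the stratification brings the benefit, not the equal totals.

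**3. Focus-group attenders.** P(2:1 or worse) = 2·P(X ≤ m/3), X ~ Binomial(m, 0.5):

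| Attenders randomised | P(2:1 or worse) |
|---|---|
| 12 | 2 × 794/4096 = 0.39 |
| 18 (midpoint, assumed) | 0.24 |
| 24 | 0.15 |

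If the 3 expert-group members come from the attenders, 9 to 21 remain and the range is 0.51 to 0.19. As a share of the whole arm the imbalance is smaller: P(share differs by 10 points or more) is 0.05 to 0.20 for 9 to 24 attenders.

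**4. Satellites.** For a site of 15 (assumed), P(2:1 or worse) = 2 × 4944/32768 = 0.30. With sites of 35, 16, 16, 15, 15 and 15 (sum 112), the chance that at least one of the six is 2:1 or worse is about 0.80.

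**5. Education.** P(differs by 10 points or more) is 0.25 to 0.30 at 30% to 50% prevalence.

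**6. Effect on the result (illustration).** If a factor shifts understanding by 0.3 to 0.8 SD (assumed), a 10-point imbalance moves the difference by 0.10 × 0.3 = 0.03 to 0.10 × 0.8 = 0.08 SD. The standard error with 112 patients is √(4/112) = 0.19 SD, so the shift is 0.16 to 0.42 of one standard error.

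**The case against.** A reader might infer that simple randomisation biases the primary comparison, or that the protocol contradicts itself. Neither is supported. The method is valid, and chance covariate imbalance is ordinary sampling variation already covered by the standard error and the type I error rate. Unequal arms look worse than they are. Most of the precision gain could also be had by covariate adjustment under simple randomisation. All of this stands.

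A reader might also infer that attenders are contaminated in the way the expert group is. The article does not say so: the focus groups discuss preferences before the method is developed, and nothing says attenders see its content. Whether they belong in the randomised comparison is a separate question, which balancing does not answer.

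Nor is restriction free in every form. The article does not say that education is on file before allocation. Crossing six sites with education and attendance would give about 14 strata for 112 patients. A plain Cork-versus-satellite stratum would leave a satellite of 15 with about a 25% chance of a 2:1 split or worse. Balance at allocation can also be partly lost through questionnaire non-response. These points limit the remedy but do not remove the case for it.

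Finally, simple may loosely mean a random half-split. Then the arm-size point disappears, but the Cork figure falls only from 0.26 to 0.22.

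**Conclusion.** The concern holds as an inexpensive improvement to design and analysis, not as an error. Because every patient is listed before allocation, chance imbalance in site and focus-group attendance is avoidable, and the unadjusted chi-square test does nothing about it.

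The size is moderate at most: about a one-in-four chance of a 10-point difference in Cork share, and a 0.39 to 0.15 chance that 12 to 24 attenders split 2:1 or worse. Each such imbalance is likely to move the result by well under one standard error. Arm-size imbalance is not part of the case.

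The Cork and attendance figures rest on counts in the article, with the 38 Cork-based patients taken as the hub site. The satellite, education and effect-size figures rest on the stated assumptions.

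**What to change.** - **Allocation.** Replace the sentence on simple random allocation: allocate the full list in one step, 1:1, within three strata (Cork attender, Cork non-attender, satellite). List satellites by site so that each is split as evenly as possible.
- **Analysis.** Adjust the primary comparison for these strata with a stratified or model-based test. Without this, most of the precision gain is not realised.
- **Education.** Add it as a stratum only if it is already on file. Otherwise use the education status collected for the planned subgroup analysis as a covariate.
- **Consistency.** Reconcile the expert-group size (three to five in section 2.1.2, 3 in Phase two), and state whether focus-group attenders are randomised.

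The cost is a slightly more complex list and a less simple test than the plain chi-square. There is no added patient burden unless education had to be collected beforehand, and concealment is unaffected. The return is modest precision and a more credible comparison.

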### Phase three: quantitative data collection

2.3

**Aim:** To measure the impact of PPI on patient understanding of end-of-trial results.

**Design:** Quantitative questionnaire evaluation of the intervention.

**Method**: A questionnaire will be developed and validated to measure patient understanding of the end-of trial results. The questionnaire will be developed in consultation with experts in the area of subclinical hypothyroidism and scale development. It is expected that the questionnaire will contain no more than 10 items which will be measured on a LIKERT scale. While there is debate in the literature regarding the minimum required sample size for exploratory factor analysis, it has been established that a ratio of 10 participants per variable is appropriate to produce solutions that are accurate representations of the population parameters [10]. Questionnaire items will be developed by adapting existing questionnaires and new items will be generated where necessary through consultation with the content and scale development experts and the patient and public expert group. Prior to administering the full questionnaire, it will be reviewed by the patient and public expert group to assess content and face validity. Any suggestions and changes made by this group will be incorporated into the final questionnaire. The questionnaire will be sent to the intervention and comparison groups one week after they have received the results of the trial.

**Analysis:** Completed questionnaires will be entered into SPSS software. The psychometric properties and construct validity of the questionnaire will be examined with exploratory factor analysis, using principal component analysis (PCA). PCA is a useful exploratory factor analytic tool that can be incorporated into the development and refinement of new scales [11]. In this case, PCA will allow for the maximum amount of variance in patient understanding to be explained by the smallest number of constructs. Internal consistency of the questionnaire will be investigated using Cronbach's alpha coefficient. Where possible, participant responses will be analysed using descriptive and inferential (Chi-square test) statistics. The researcher carrying out the input and analysis of this data will be blinded to the participants' allocation status. Subgroup analysis will also be conducted to measure how patient understanding is impacted by age, gender, education status and study site attended.

**Outcome:** The primary outcome will be difference in levels of patient understanding between the intervention and comparison groups. This will measure the impact of PPI on patient understanding of end of trial results.

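### No single score is fixed for the primary outcome, and the only named test, a chi-square on Likert responses, ignores the order of the categories and estimates no difference in level

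*Protocol article*

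**What the plan says.** All of this is in the protocol article, mainly section 2.3 (Phase three: quantitative data collection).

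- Outcome: "The primary outcome will be difference in levels of patient understanding between the intervention and comparison groups". No total, mean or component score, cut-off or key item is attached to it.
- Instrument: "It is expected that the questionnaire will contain no more than 10 items which will be measured on a LIKERT scale". The number of response levels is not given.
- Scale development: a principal component analysis and Cronbach's alpha are planned, on the ground that "PCA will allow for the maximum amount of variance in patient understanding to be explained by the smallest number of constructs". Neither step is linked to a score used to compare the arms.
- Test: "Where possible, participant responses will be analysed using descriptive and inferential (Chi-square test) statistics". No other inferential test is named, and no effect measure.
- Numbers: the Population paragraph of section 2 gives 115 Irish participants. Section 2.2 adds that "Participants from the patient and public expert group (n = 3) will not be randomised". Allocation is by simple randomisation, with no ratio stated.

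**The concern.** The outcome and the test do not fit each other. A difference in level is an ordered quantity with a size and a direction. A Pearson chi-square on a table of several response levels asks only whether the two distributions differ in any way: its result is unchanged if the columns are shuffled. The planned descriptive statistics could show which way the answers lean, but no estimate with an interval is named for the one comparison the study exists to make.

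The plan also builds a multi-item scale and then describes the comparison in terms of responses, without saying that the scale score is used. With no score fixed, the primary result could be taken from any of several items, components or cut-offs after the answers are known. With at most 112 people randomised, the study can ill afford a test that sets aside information it has collected.

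**Working it through.** **Inputs from the article.** At most 10 Likert items; 115 participants less 3 not randomised; chi-square as the test.

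**Assumptions not in the article.** Two-sided alpha 0.05, 1:1 allocation, five response levels, the shares of answers in each level, the correlation between items, the size of the true shift, and the return rate.

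**1. The plan's own sizing figure.** The article relies on a rule for factor analysis: "it has been established that a ratio of 10 participants per variable is appropriate". With 10 items this needs 10 × 10 = 100 replies. Randomised: 115 − 3 = 112, or 112/10 = 11.2 per item. The rule is met if at least 100/112 = 89.3% reply. The figure reproduces, but it concerns the factor analysis and says nothing about the comparison of arms.

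**2. Arm sizes used below.** Full return: 112/2 = 56 per arm. About 70% return: 0.70 × 112 = 78.4, so about 39 per arm.

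**3. False positives if each item is tested and any one counts.** For k independent tests at 0.05 the chance of at least one is 1 − 0.95^k:

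- k = 5: 0.226
- k = 8: 0.337
- k = 10: 0.401

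Simulation with 10 five-level items, latent correlation 0 to 0.5, 39 or 56 per arm and 2,000 replicates gives 0.305–0.341 for skewed answers (3/7/15/45/30%). For evenly spread answers, at correlation 0.3, it gives 0.396–0.400. A single t-test on the total score stays at 0.047–0.060 in the same runs.

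**4. Power with a true shift of 0.4 SD on every item** (shares 5/10/20/40/25%, correlation 0.3–0.5; repeat runs differ by a point or two):

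| Analysis | 39 per arm | 56 per arm |
|---|---|---|
| Chi-square, one item | about 19% | 26–31% |
| Ten chi-squares with Bonferroni | 20–23% | 37–39% |
| Rank test, same single item | 33–37% | 48–50% |
| t-test on total score | 64–80% | 79–90% |

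With a 0.5 SD shift and correlation 0.3 the pattern is the same. At 39 per arm, power is 27–34% for one chi-square, 48–53% for a rank test on that item and 92–95% for the total. At 56 per arm the figures are 41–47%, 66–70% and about 98%. Comparing chi-square with the rank test on the same item isolates the cost of ignoring order: roughly 15 to 25 percentage points.

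The uncorrected any-item rule also detects a 0.5 SD shift often (89–98%), but only at the false-positive rate in step 3.

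**5. Sparseness.** For an expected count of 5 per arm, a level needs a pooled share of at least 10/N: 8.9% at N = 112 and 12.8% at N = 78. Even answers over five levels give 112/10 = 11.2 or 78/10 = 7.8 per cell. Shares of 3/7/15/45/30% give 56 × 0.03 = 1.7 and 56 × 0.07 = 3.9 in the two lowest levels at full return. With shares 5/10/20/40/25% and no effect, the proportion of item tables with over 20% of expected counts below 5 is about 76% at 39 per arm and 29% at 56. With even shares it is under 1%. In the skewed runs of step 3 the per-item error rate was 0.036–0.043, so sparseness made the test slightly conservative, not liberal.

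**The case against.** The strongest reply is that a condensed article may leave scoring and multiplicity to a fuller document. That holds for a scoring algorithm or a correction rule. It does not remove the point, because the article is not silent on the comparison: it names a test, and that test does not suit the outcome it states.

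Several stronger readings are tempting, and the text does not support them.

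- **A reader might infer up to ten uncorrected primary tests.** The article does not say that items are tested one by one, that each is primary, or that one significant item means success. A chi-square on a categorised total or component score is also compatible with the wording, although no cut-off is given and categorising would lose information. The 31–40% is therefore conditional.
- **A reader might infer that the tables will be sparse.** That depends on the number of levels, the spread of answers and the return rate, none of which is stated.
- **A reader might take the qualifier at the start of the test sentence to mean that the data decide what is tested.** The article does not say what it refers to.
- **A reader might conclude that the scale score is never used.** The article only fails to say that it is. The remark about reducing understanding to few constructs suggests that construct scores may have been in mind.

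On the figures, an identical shift on every item favours the total score, so the power gap would be smaller if only some items moved. The loss from ignoring order does not depend on that assumption, since it appears within a single item.

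**Conclusion.** The concern stands in limited form. The primary outcome has no fixed score, and the only test named ignores the order of the responses and yields no effect estimate. Both follow from the text without assumptions.

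The sizes are conditional. The inflated error rate requires uncorrected item-by-item testing of 10 items. The power contrast requires five levels, the assumed answer pattern and correlation, and an equal shift on all items; it shows an order of magnitude and is not a forecast for this study. Sparse tables are a possibility only, and where simulated they did not add false positives.

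**What to change.** Before any unblinded data are seen, name one summary score as the primary outcome: the total or mean over the items, or a component score whose construction is fixed without reference to allocation. Compare the arms on it with one test and report the mean difference with its 95% confidence interval. Make item-level comparisons secondary or descriptive, and use an ordinal method (Wilcoxon or proportional odds) in place of chi-square.

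Adjustment for age, gender, education or site is optional and not part of this fix; the article mentions those factors only for subgroup analysis.

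The cost is a change of wording: the questionnaire and the data stay the same. The downside is that the result then rests on the items being summable, which the planned principal component analysis and Cronbach's alpha will check.

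### As written, the primary arm comparison uses neither the ordering of the understanding score nor the patient characteristics already planned for, which costs efficiency (not validity) in a sample fixed at about 110 to 112

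*Protocol article*

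**What the plan says.** Section 2.3 defines the primary outcome: "The primary outcome will be difference in levels of patient understanding between the intervention and comparison groups". It gives no effect measure and no model. On method, the Analysis paragraph says: "Where possible, participant responses will be analysed using descriptive and inferential (Chi-square test) statistics". No other between-group test is named. The instrument is to have at most 10 Likert items.

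Age, gender, education and site enter in one sentence: "Subgroup analysis will also be conducted to measure how patient understanding is impacted by age, gender, education status and study site attended". They are given no role in the arm comparison.

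The size is inherited from the host trial. Under Population: "As this is a SWAT within the TRUST trial, the study sample is determined by the trial", with 115 Irish participants. Section 2.2 then removes the expert group: "Participants from the patient and public expert group (n = 3) will not be randomised". Section 2.1.2 puts that group at three to five people. Allocation is simple, and no stratification is mentioned.

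**The concern.** An ordinary chi-square test treats response categories as unordered and takes no covariates. The outcome is built from ordered Likert items. The four patient characteristics are fixed before allocation, so they can enter the arm comparison without introducing bias. The plan must hold them in any case to run its subgroup analysis.

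More recruitment is not available, so precision has to come from the analysis. Two sources are open at almost no cost: treating understanding as a score, and adjusting for characteristics that may explain part of it. The stated method uses neither. What is at stake is the width of the interval and the power for the primary outcome. Simple allocation adds a smaller reason to adjust, because balance on these characteristics is left to chance.

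**Working it through.** The article gives no power calculation, alpha, SD, effect size or response rate, so there is no stated figure to reproduce beyond the sample size.

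**Inputs from the article.** 115 participants, less 3 expert-group members: 115 − 3 = 112. With five members, 115 − 5 = 110. There are six sites: one hub and five satellites.

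**Assumptions, not in the article.** Equal arms (56 each), two-sided 5% level, a total score scaled to SD 1, and covariates explaining R² = 10%, 20% or 30% of its variance. A return rate of 70% gives 0.70 × 112 ≈ 78 questionnaires.

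**Covariate degrees of freedom.** Linear age 1, gender 1, education in two categories 1, Cork versus satellite 1: q = 4.

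**Formula.** Variance ratio, adjusted to unadjusted = (1 − R²)(n − 3)/(n − q − 3). The equivalent gain in patients is 1/ratio − 1.

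- n = 112, q = 4: (n − 3)/(n − q − 3) = 109/105 = 1.038.
- n = 78, q = 4: 75/71 = 1.056.

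| R² | Ratio, n = 112 | Gain | Ratio, n = 78 | Gain |
|---|---|---|---|---|
| 0 | 1.038 | −4% | 1.056 | −5% |
| 10% | 0.934 | +7% | 0.951 | +5% |
| 20% | 0.830 | +20% | 0.845 | +18% |
| 30% | 0.727 | +38% | 0.739 | +35% |

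At n = 110 the ratios are almost the same (0.935, 0.831, 0.727). A simulation of 6,000 runs at n = 112 gave 0.95, 0.84 and 0.73.

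**Interval.** The unadjusted half-width is 1.96 × 2/√112 = 0.37 SD. Multiplying by the square root of each ratio gives about 0.36, 0.34 and 0.32 SD.

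**Power at an assumed difference of 0.5 SD, n = 112.** Unadjusted 75.4%; adjusted with 4 df 73.8%, 78.1%, 82.7% and 87.4% for R² of 0, 10%, 20% and 30%.

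**Break-even.** Adjusting helps once R² exceeds 1 − 105/109 = 3.7% at n = 112, or 1 − 71/75 = 5.3% at n = 78.

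**How site and education are coded.**
- Six site levels with two-category education use 8 df. At R² = 10% the ratio is 0.9 × 109/101 = 0.971 (+3%) at n = 112 and 0.9 × 75/67 = 1.007 (−1%) at n = 78.
- Six site levels with three-category education use 9 df. The ratios are 0.981 (+2%) and 1.023 (−2%).
- Cork versus satellite with three-category education uses 5 df. At n = 112 the gains are 6%, 19% and 36%.

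**Score against chi-square.** In simulation (n = 112, 0.5 SD, 4,000 runs per setting), a t-test on the score had 73–75% power. A chi-square on the same score split near its middle had 54–55%. That gap of about 20 points exceeds the 87.4 − 75.4 = 12 points from adjustment at R² = 30%.

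**Chance imbalance.** With simple allocation of 112, a characteristic held by half the patients differs by at least 10 percentage points between arms in about 30% of randomisations.

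**Ordinal alternative.** A small simulation (60 runs per setting, n = 112, five categories, four covariates, latent R² 10%, 20%, 30%) gave standard errors of the log odds ratio of 0.344, 0.344 and 0.342 unadjusted, and 0.357, 0.359 and 0.365 adjusted. The interval does not narrow there.

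**The case against.** The strongest reply is that this is a condensed article, and the covariate set is commonly left to an analysis plan. The article does not say that the primary comparison will be unadjusted, and the chi-square sentence concerns questionnaire responses in general and is qualified. That stands in part: a reader might infer that adjustment is ruled out, and the text does not go so far. But the article is not merely silent. It names one test and gives the covariates a different job, and those stated choices can be questioned.

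Four stronger readings are tempting, and the documents do not support them.

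- *The result would be biased.* Under random allocation an unadjusted comparison is valid. Only efficiency is at issue.
- *The plan already treats these factors as explaining understanding.* It sets out to examine how they bear on it. No R² is given, and at 10% the half-width moves only from 0.37 to 0.36 SD.
- *Covariates are the only free source of precision.* Moving from a chi-square on a split score to a score-based analysis can gain more. Even so, the article does not say that the score will be split, so the 20-point figure illustrates one way of using the test.
- *The factors will be examined one at a time.* The text does not say whether they are examined singly or together.

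It is also fair to object that the patient-equivalent gains belong to a linear model. They do not carry over to a proportional-odds model, where adjustment changes the target to a conditional odds ratio and may widen its interval even when power rises.

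**Conclusion.** The point holds as one of efficiency. The only named test uses neither the ordering of the outcome nor the four characteristics, and the sample is capped at about 110 to 112. For a total score with 4 covariate df, adjustment is worth about 7%, 20% or 38% more patients at 112, and 5%, 18% or 35% at 78 returns, if R² is 10%, 20% or 30%. Those R² values, equal arms and the 70% return rate are assumptions. The gain depends on a short covariate set: coding all six sites removes most of it at R² = 10%. The planned primary comparison would be less precise than it could be, but not invalid. The change is worth making but is not essential to a sound trial.

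**What to change.** Name the primary analysis as a linear model of the total understanding score on arm, with age (continuous), gender, education (few categories), and Cork versus satellite site, all fixed before the data are seen. Report the adjusted mean difference with its 95% CI as the primary result. Keep the unadjusted difference and the chi-square as supportive.

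If an ordinal outcome is preferred, use a proportional-odds model with the same covariates. State that it estimates a conditional odds ratio, that power may rise, and that the interval need not narrow.

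Keep the subgroup analysis separate, because a main-effects model does not replace it. If the question is whether the effect of the dissemination method differs by subgroup, specify arm-by-factor interactions.

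The cost is analysis wording only, since the subgroup analysis already requires these variables. If the covariates explain nothing, variance rises by about 4% at 112 and 6% at 78.
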